### Interventions

Participants are randomized into either one out of the three approaches (exp. I–III). Three randomizations take place—one for each experiment. Patients are randomly assigned to receive either first verum then placebo, or vice versa. The randomization lists were created using RANCODE professional 2015. Randomization is performed block-wise. The randomization list was provided to the pharmacy for blinding, labelling and distribution of trial medication. For the case of emergency unblinding, a second set of sealed envelopes includes the information on the type of medication for each randomization number and is stored at the trial site. The integrity of the envelopes is monitored until end of study.

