#### Experiment I—Lamotrigine (LTG) in patients with NS

Participants receive 300 mg single dose LTG or placebo 2 h before TMS, corresponding to the peak plasma time of LTG [11]. After at least 7 (up to 60) days, a cross-over takes place: participants receive placebo or 300 mg single dose LTG 2 h before TMS (Fig. 1).

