### Endpoints and endpoint rationale

The *primary endpoint* for each experiment is the difference between the amplitude of the motor evoked potential (MEP) elicited with transcranial magnetic stimulation (TMS, measured at three time points after interventional TMS for each investigation) after placebo and after medication (LTG and LOV).

Changes in MEP are a well-established and safe method to probe changes in cortico-spinal excitability in humans [18]. MEPs are elicited by TMS using a figure-of-eight coil with an outer diameter of 100 mm centred tangentially on the scalp over the primary motor cortex (M1) of the nondominant hand with its handle pointing in a posterior direction and laterally at an angle of approximately 45° away from the midline. MEPs are recorded from the abductor pollicis brevis (APB) muscle at rest by surface electromyography (EMG) using silver/silver chloride electrodes with a surface area of 263 mm^2^ (AMBU, Ballerup, Denmark) mounted in belly-tendon recording technique. Data are band-pass filtered (20–2000 Hz) and amplified using an Ekida DC universal amplifier (EKIDA GmbH, Helmstadt, Germany), digitized at 5 kHz sampling rate using a MICRO1401*mkII* data acquisition unit (Cambridge Electronic Design Ltd, Cambridge, UK) and stored on a standard personal computer for online visual display and later offline analysis using Signal Software version 5 (CED Ltd, UK). MEP size is determined by measuring the two highest peaks of opposite polarity. Twenty trials will be recorded and then averaged for each point of investigation as described elsewhere [15, 16]. Resting motor threshold is recorded to probe changes in local cortical excitability [19].

The *secondary endpoints* for each experiment include the difference between the neuropsychological testing of attention by the TAP and differences in short interval cortical inhibition (SICI) after placebo and after medication (LTG and LOV) [6, 20]. Another endpoint is the comparison of LTG and LOV effects on synaptic plasticity and attentional performance in the NS group. The TAP is a well-established tool and used to measure the influence of LTG and LOV on attention [7, 20]. We previously demonstrated that LOV leads to an amelioration of attentional performance in humans with NF1 [6]. Consequently, we hypothesized that this would also lead to better attention in patients with NS and that LTG ameliorates attention in NF1 and NS.

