**Experiment III**			
Local α	0.050	0.025	0.017
Power with 14 patients	94%	97%	99%
Power with 12 patients	90%	94%	97%

An increase in MEP amplitudes over time is considered to refer to the concept of long-term potentiation (LTP)-like plasticity as it has been demonstrated in Mainberger et al. [7] as well. Twelve patients per disease entity will be enough to provide appropriate power to all planned primary endpoint tests (two-sided paired samples *t*-tests) with a global significance level of 5% and adjusted local significance levels using the Bonferroni-Holm procedure. In order to account for some unobtainable data and drop outs, the sample size will be increased to 14 patients per disease (28 trial participants in total).

Analysis sets: For each experiment, there will be a separate analysis set defined, as it is possible that a patient is suitable for analysis in only one of the first two experiments. All analyses will be performed on the full analysis set (FAS-I, FAS-II, FAS-III), consisting of all patients who delivered a full set of MEP measurements within the corresponding experiment. Since all measurements will take place within a very short time per patient, it is expected that the data will be either complete or entirely missing.

Primary endpoint: The primary endpoint analyses will be performed in three separate testing procedures. The global significance level will be 5%. Since experiments I and II are done on the same set of patients, the significance level for those two experiments will each be 2.5%. The significance level of experiment III will be 5%. The primary endpoint analysis will consist of three series of three paired samples two-sided* t*-tests, comparing MEP under verum vs. placebo at the three measurement time points. The local significance level will be adjusted using the Bonferroni-Holm procedure and will be as follows for the ordered by *p*-value tests:

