**Table Tabb:** 

Experiment	Test number	Local significance level
I and II	1	0.025
I and II	2	0.013
I and II	3	0.008
III	1	0.050
III	2	0.025
III	3	0.017

Secondary endpoints and safety: Analyses of baseline and safety data and secondary endpoints will be done using appropriate descriptive statistics and paired sample tests for difference between the two study groups. All tests will be two-sided with an exploratory significance level of 5%. No adjustment for multiple comparisons will be done.

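### Plain paired tests ignore the randomised sequence: a period effect costs power when sequences are equal and biases the estimate when they are not

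*Protocol article*

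**What the plan says.** The section *Interventions* sets up a standard two-sequence cross-over, randomised separately for each experiment: "Patients are randomly assigned to receive either first verum then placebo, or vice versa". It adds: "Randomization is performed block-wise". The block size is not given. For Experiment I the gap between periods is 7 to 60 days ("After at least 7 (up to 60) days, a cross-over takes place"), and Experiment III has the same gap.

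Under *Analyses and statistics*, the primary endpoint paragraph reads: "The primary endpoint analysis will consist of three series of three paired samples two-sided" t-tests, comparing MEP under verum and placebo at the three time points. The sample size table is built on the same test. For the secondary endpoints, which include TAP and SICI, the plan is "paired sample tests for difference between the two study groups", at an exploratory 5% level. Neither paragraph has a term for period or sequence.

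Three further facts bear on the point:

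- Tables 1 and 2 schedule TAP at every TMS visit, so four times in the NS group and twice in the NF1 group.
- Each full analysis set contains only patients with complete MEP data for that experiment.
- *Trial status* reports early closure with 16 participants enrolled, against 28 planned.

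**The concern.** In a cross-over, the verum-minus-placebo difference of a patient who took verum second contains the drug effect plus any period shift. For a patient who took verum first it contains the drug effect minus that shift. Randomising the order makes the two separable, but only if the analysis uses the order. A plain paired t-test pools both kinds of patient. With equal sequences the shift cancels from the mean but stays in the standard deviation. With unequal sequences part of it also stays in the mean.

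A shift is plausible for TAP, a battery of reaction-time and response-inhibition tasks that each patient repeats. For MEP, the documents offer no mechanism beyond sessions that lie days to weeks apart. Equal sequences are not assured, because the analysis sets hold completers only and recruitment stopped early. At stake is power in a very small trial and, under imbalance, an estimate that mixes drug and period.

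**Working it through.** **Inputs from the sample size table.** T1 difference 0.52; SD 0.5; local level 0.025 at T1 for Experiments I and II and 0.05 for Experiment III; 12 or 14 patients.

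**Reproducing the plan's power.** For a two-sided paired t-test, the noncentrality is (difference/SD) × √n with n − 1 degrees of freedom. At T1 with n = 12 this is (0.52/0.5) × √12 = 1.04 × 3.464 = 3.60.

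| Setting | Plan | Recomputed |
|---|---|---|
| Exp. I/II, n = 12, T1 | 82% | 82.6% |
| Exp. I/II, n = 14, T1 | 89% | 89.6% |
| Exp. III, n = 12, T1 | 90% | 90.6% |
| Exp. III, n = 14, T1 | 94% | 94.9% |

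The plan's figures therefore treat 0.5 as the SD of the paired difference and assume no period effect.

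**Model with a period shift.** Write d = τ + s·δ + e, where s = +1 if verum came second and −1 if it came first, and e has SD 0.5. Let n1 be the number with s = +1 and n2 the number with s = −1. δ is an assumption; it is shown at 0.5 SD (0.25) and 1 SD (0.5).

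- Bias of the plain estimate, given the split: δ·(n1 − n2)/n.
- Expected variance used by the plain test: SD² + δ²·[n/(n − 1)]·[1 − ((n1 − n2)/n)²].
- Period-adjusted estimate: the average of the two sequence means of d, with standard error SD·½·√(1/n1 + 1/n2) and n − 2 degrees of freedom.

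**Equal sequences, 6/6.** At δ = 0.25 the expected variance is 0.25 + 0.0625 × 12/11 = 0.318, against 0.25 without a shift. The adjusted standard error at 6/6 is 0.5 × ½ × √(1/6 + 1/6) = 0.144, the same as 0.5/√12, so only one degree of freedom is lost. Power at T1, level 0.025 (plain test by simulation):

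| Shift δ (SD units) | Plain paired test | Period-adjusted |
|---|---|---|
| 0 | 82.7% | 81.5% |
| 0.5 | 73.8% | 81.5% |
| 1 | about 47% | 81.5% |

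**Unequal sequences: bias of the plain estimate.**

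- 7/5: δ × 2/12 = 0.17δ
- 5/3: δ × 2/8 = 0.25δ
- 8/4: δ × 4/12 = 0.33δ
- 6/2: δ × 4/8 = 0.5δ

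The splits of 8 patients assume that the 16 enrolled divide evenly between NS and NF1, which the article does not say.

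**Type I error of the plain test at nominal 5%.**

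| Split | δ = 0.5 SD | δ = 1 SD |
|---|---|---|
| 4/4 | 3.1% | 0.7% |
| 5/3 | 3.9% | 1.9% |
| 6/6 | 2.9% | 0.6% |
| 7/5 | 3.7% | 1.5% |
| 8/4 | 5.6% | 5.1% |
| 6/2 | 6.8% | 8.5% |

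**Price of adjusting when there is no period effect.** At the 5% level, plain against adjusted power is 90.6% and 90.0% at 6/6, about 71.5% and 69% at 4/4, 71.4% and 66.3% at 5/3, and 71.4% and 56.9% at 6/2.

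**The case against.** The strongest defence has four parts.

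1. **No period effect is documented** for MEP, SICI or TAP, and the most credible one, TAP practice, affects an exploratory secondary endpoint. This stands. All losses above depend on an assumed δ, and for the primary endpoint the case is one of design logic, not of evidence.

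2. **Block randomisation limits imbalance**, and over repeated randomisation the plain estimate is unbiased. This stands too. The bias is conditional on the realised split, and nothing shows that a split such as 6/2 occurred. It does not answer the power loss, which arises with perfectly equal sequences.

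3. **Adjustment is not free.** In small or unequal sequences it costs several points of power if there is no shift. That is correct, and the cost is given below.

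4. **The analysis plan, not shown here, could add a period term.** It could, but the article names the paired t-test as the primary analysis and powers the trial on it. That is a stated choice, not a detail left open.

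A reader might infer that the trial is likely to report a practice effect as a positive drug effect. The figures do not support that. At 4/4, 5/3, 6/6 and 7/5 the plain test is conservative, and at 8/4 it is near nominal.

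A reader might also say that the lamotrigine–lovastatin comparison suffers from the same defect because Experiment I always comes first. The article lists this comparison ("Another endpoint is the comparison of LTG and LOV effects on synaptic plasticity and attentional performance in the NS group") without giving a method. Each experiment has its own placebo, so with balanced sequences a placebo-corrected contrast removes a common shift with visit order. What remains, such as an interaction of order with treatment, is a limitation of the fixed order and not a missing period term.

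The reference to two study groups in the secondary-endpoint paragraph is a slip of wording. The pairing and the endpoint definitions make the within-patient contrast clear.

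**Conclusion.** The point holds as a matter of efficiency and of conditional bias. The randomised sequence is known for every patient, yet the stated tests for MEP, TAP and SICI do not use it. If a period shift of 0.5 to 1 SD of the paired difference exists, power at T1 with 12 patients in Experiments I and II drops from 83% to between 74% and about 47%, where an adjusted test would keep about 81%. If sequences end up unequal, the plain estimate carries 0.25δ at 5/3 and 0.5δ at 6/2. Inflation of the type I error is a concern only for extreme splits.

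The algebra is certain. The practical size is not, since it rests on an undocumented δ, on 0.5 being the SD of the paired difference, and on unknown realised sequence sizes. The change should be made, but the point does not invalidate the trial.

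**What to change.** Make the period-adjusted cross-over analysis the main one for MEP, SICI and TAP: compare the within-patient period differences between the two sequences with a two-sample t-test, or fit a mixed model with treatment, period and patient. Keep the plain paired t-test as a sensitivity analysis, and report the realised sequence sizes for each analysis set.

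For lamotrigine against lovastatin, specify the placebo-corrected, period-adjusted contrast and state that the fixed order of experiments remains a limitation. In the secondary-endpoint paragraph, describe the contrast as verum against placebo within patient.

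No new data are needed, because the randomisation lists hold the sequence. The statistical cost if there is no period effect, at the 5% level, is under 1 point of power at 6/6, about 2.5 at 4/4, 5 at 5/3 and 14 at 6/2. At the 2.5% level of Experiments I and II it is somewhat higher (about 1 point at 6/6, 3 at 4/4, 6 at 5/3 and 15 at 6/2). The choice should be fixed before treatment codes are linked to outcomes, not after seeing the split.

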**Table Tabb:** 

Experiment	Test number	Local significance level
I and II	1	0.025
I and II	2	0.013
I and II	3	0.008
III	1	0.050
III	2	0.025
III	3	0.017

Secondary endpoints and safety: Analyses of baseline and safety data and secondary endpoints will be done using appropriate descriptive statistics and paired sample tests for difference between the two study groups. All tests will be two-sided with an exploratory significance level of 5%. No adjustment for multiple comparisons will be done.

### Organizational framework

Organizational/regulatory project management, safety management, monitoring and data management are performed by the Münchner Studienzentrum (MSZ), Technical University of Munich, School of Medicine. An independent safety monitoring board (SMB) is established. The underlying principles for the SMB are ethical and safety aspects for the patients. The SMB examines whether the conducting of the study is still ethically justifiable, whether safety of the patients is ensured and whether the process of the study is acceptable. For this, the SMB is informed regularly about patient recruitment and observed safety advents. Serious adverse events (SAEs) are recorded in a study-specific safety form and transferred into a safety database by the safety management, which processes further SAE documentation in written form to the SMB, the Investigator, the ethics committee and regulatory authority (BfArM) according to applicable law.

All study procedures agree with the guidelines of Good Clinical Practice (GCP) of the International Council on Harmonization of Technical Requirements for Pharmaceuticals for Human Use (ICH) and the principles of the Declaration of Helsinki. All participating investigators agreed to adhere to the instructions and procedures described in the study protocol and thereby to adhere to the principles of ICH-GCP. All members of the safety board are independent from the sponsor. The current approved protocol version is 5.0 (amendment 3, 21.09.2020). All protocol versions are available in German language at [contact].

## Discussion

The SynCoRAS study is targeting impairments in synaptic plasticity and cognitive impairment, one of the main health problems of patients with RASopathies. This has been done by the authors successfully for Lovastatin in NF1 before [6]. The obtained results will be transferred to patients with Noonan syndrome which demonstrated a reduced plasticity before as well [7]. Lamotrigine is most likely a more effective and promising substance improving synaptic plasticity and, consecutively, cognitive function [5, 10]. It is expected that both substances are improving synaptic plasticity as well as alertness. Changes in alertness may be a precondition for improvement of cognition. The strength of this project may be the short-term translation of results of basic science to human application and the provision of insights in pathophysiological mechanism. Results will be brought to practice through the tight connection to the large clinical centre for patients with cognitive impairment. Results might be used for the treatment of patients on an individual level as well as for the initiation of large clinical trials.

### Risk/benefit analysis

There are known side effects of lovastatin (LOV) and lamotrigine (LTG). LOV and LTG are used in an off-label context and in a higher dosage as recommended in the Summary of Product Characteristics (SMPC) of the medicinal products. However, all side effects of the medication (LOV and LTG) have been described after longer application whereas in the present study patients will receive LOV only four times and LTG only one time. In one patient receiving LTG, a mild rash following the administration reported has been reported [21]. In an own placebo-controlled, randomized, double-blind study using the same single dose of LTG (300 mg), no side effects, apart from mild sedation/dizziness and lacrimation have been reported in 26 young healthy adults [10]. LTG has been well tolerated in another TMS study using dosages up to 325 mg [11]. Severe skin reactions such as Stevens-Johnson syndrome, toxic epidermal necrolysis, drug rash with Eosinophilia and systemic symptoms (DRESS) syndrome or aseptic meningitis occurring 8 weeks after long-term application of LTG have never been mentioned after single-dose application. These adverse events can be excluded to the actual state of knowledge.

A 4-day course of LOV has been used in an own study in *n* = 11 patients with NF1 and is not expected to provoke any side effects [6]. It has been shown that doses of 200 mg of LOV were proven to be save in adult human volunteers [22]. Moreover, accidental overdoses up to 6 g have been tolerated with no specific symptoms and recovery without sequelae. Adverse events of LOV occur after longer application (> 1–2 weeks). Overall, the treatment with LTG and LOV in the context of the present study is not expected to provoke any side effects. A randomized, placebo-controlled long-term study investigated the effect of simvastatin, another 3-hydroxy-3-methyl-glutaryl-coenzyme A (HMG-CoA) reductase inhibitor, on cognition in children with NF1 [23]. This study did not find effects of simvastatin on cognition in children with NF1 [23]. In the present study, LOV will be used to investigate its effects on synaptic plasticity and attentional performance in patients with NS. We previously demonstrated in a randomized, placebo-controlled trial effects of LOV on synaptic plasticity and attentional performance in patients with NF1 in short-term use [6]. Moreover, another study demonstrated effects of lovastatin in children with NF1 undergoing a dose escalation protocol for 3 months on verbal and nonverbal memory [24]. This may highlight potential pharmacological differences of LOV and simvastatin.

The results of the present study may help to design long-term studies focusing on the therapeutic effects of LTG on synaptic plasticity and cognition in patients with NF1. It is intended to publish the results in an international scientific journal. The inclusion of minors from the age of 16 years is not considered to increase the risk of potential side effects since persons are considered to be grown-up at this age from a medical point of view. We do not expect significant differences in body weight or in the metabolism of both medications (LTG and LOV) in adolescents aged 16 years why an adaption of the dosage is not necessary. LTG is a safe and commonly used medication in the treatment of seizures/epilepsy in children and adolescents. For medications (LTG and LOV), the risk of side effects after a single dosage (LTG) and a 4-day course of LOV is not considered to be increased in adolescents. Moreover, we estimate the benefit of an early treatment of attention deficits with the medication to be higher than the risk of the treatment in this study. Side effects associated with LTG or LOV are closely monitored and handled as described above. In case of acute threatening of the patients, treatment will be handled as described in the emergency plan of the hospital.

### Trial status

The current protocol version number is “Final 5.0 AM 3.0”, date 9/21/2020. Recruitment finished on 3/30/2023 prematurely due to unforeseen difficulties in recruitment of patients. Recruitment was still open on initial submission of the manuscript. Recruitment began in March 2018, and an actual number of 16 participants have been enrolled. A large panel including the sponsor-delegated person, the head of German Network of RASopathy Research (GeNeRARe) and the Sponsors representative for risk-based quality management decided to prematurely close the recruiting and to terminate the study in retrospect on 2/20/2023 due to the last patient last visit (LPLV) taking place on 2/9/2023.

## Conclusion

In summary, we aim to investigate the effects of LTG and LOV on synaptic plasticity and cognitive function in patients with NS and LTG in patients with NF1. The results may provide significant information about the effectiveness and the mode of action of these interventions in humans and may help to design larger multicentre clinical trials. The strength of the project may be the short-term translation of results of basic science in the setting of a large hospital with a high reputation in medical care of patients with cognitive disorders.

## Data Availability

Anonymized datasets that will be analysed during the current study will be available from the corresponding author on reasonable request.

## Abbreviations

AE: Adverse event
APB: Abductor pollicis brevis
BfArM: Bundesinstitut für Arzneimittel und Medizinprodukte
BW: Body weight
CFC: Cardio-facio-cutaneous syndrome
CNS: Central Nervous System
CRF: Case Report Form
CS: Costello syndrome
CTCAE: Common terminology criteria for adverse events
DRESS: Drug rash with Eosinophilia and systemic symptoms
GCP: Good Clinical Practice
eCRF: Electronic Case Report Form
EMG: Electromyography
ER: Emergency Room
EU: European Union
FAS: Full analysis set
FPFV: First Patient First Visit
GABA: Gamma-aminobutyric acid
GCP: Good Clinical Practice
HMG-CoA: 3-Hydroxy-3-methyl-glutaryl-coenzyme A
ICH: International Council on Harmonization of Technical Requirements for Pharmaceuticals for Human Use
ITT: Intention to treat
LTG: Lamotrigine
LTP: Long-term potentiation
LPFV: Last Patient First Visit
LPLV: Last Patient Last Visit
LOV: Lovastatin
M1: Primary motor cortex
MAPK: Mitogen-activated protein kinases
MEP: Motor Evoked Potential
MSZ: Münchner Studienzentrum
NS: Noonan Syndrome
NF1: Neurofibromatosis type 1
PP: Per protocol
PLC: Placebo
RAS: Rat sarcoma
SAE: Serious adverse event
SD: Standard deviation
SICI: Short interval cortical inhibition
SMB: Safety monitoring board
SMPC: Summary of Product Characteristics
SUSAR: Suspected unexpected serious adverse reactions
TAP: Test of Attentional Performance
T1-3: Timepoint 1–3
TMS: Transcranial Magnetic Stimulation
QPS: Quadri-pulse stimulation
qTBS: Quadri-pulse theta burst stimulation
